### Procedure

Potential participants will first undergo screening to determine eligibility, including assessment of medical history and lifestyle habits. Individuals meeting the eligibility criteria will be invited to an in-person visit, during which the study procedures will be explained and written informed consent will be obtained.

All baseline assessments will be completed on a single day following participant enrolment. Upon arrival at the hospital, participants will complete questionnaires collecting demographic and clinical information, including sex, age, height, weight, marital status, home address, and contact information. Body composition measurements and physical fitness tests will then be performed to assess mobility, muscle strength, and overall physical function. Participants will also complete supplementary questionnaires at home covering dietary status, quality of life, and SO-related symptoms.

After baseline assessment, trained research staff will assist participants in the intervention group with downloading and using the SO-KGCS system. Based on baseline assessment results, the system will provide personalized plans for nutrition, exercise, and lifestyle modification. Participants in the intervention group will receive regular personalized updates through the system, while those in the control group will receive standard health education. The intervention period will last 24 weeks. During the study, all participants will be instructed to maintain a daily calorie intake approximately 200 kcal below their baseline levels, in accordance with the ESPEN and EASO Consensus Statement on SO. Daily protein intake will be maintained at ≥1.2 g/kg body weight.

All assessments will be performed by uniformly trained professional nurses using standardized procedures. After baseline assessment and randomization at week 0, outcome assessments will be conducted at weeks 8, 16, and 24, with week 24 defined as the end of the intervention. A final follow-up assessment will be conducted at week 48, corresponding to 24 weeks after completion of the intervention. Adherence, adverse events, and reasons for withdrawal will be recorded throughout the intervention period.

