### Statistical analysis

The primary efficacy analysis will be conducted according to the ITT principle, with all randomized participants analyzed in the groups to which they were originally assigned. Continuous variables will be summarized as means ± standard deviations or medians with interquartile ranges, as appropriate based on distribution, and categorical variables will be presented as frequencies and percentages. Baseline characteristics will be summarized by treatment group. Between-group comparisons at baseline will be performed using independent-samples *t* tests or Mann-Whitney U tests for continuous variables, and χ² tests or Fisher’s exact tests for categorical variables.

The primary analysis population will be the ITT population. A per-protocol set analysis will be conducted as a sensitivity analysis and will include participants who complete the intervention and follow-up assessments, meet prespecified adherence criteria, and have no major protocol deviations. Poor adherence will be defined as an intervention adherence rate of <50% per week for two consecutive weeks or an overall intervention adherence rate of <50% during the study period. The safety analysis population will include participants who receive at least one intervention session or complete at least one post-randomization safety assessment.

The sole primary confirmatory outcome will be SMM. The primary intervention effect will be defined as the adjusted between-group difference in change in SMM from baseline to the end of the 24-week intervention. The primary outcome will be analyzed using a linear mixed-effects model, with post-randomization SMM measurements as the dependent variable. Fixed effects will include group, time, the group-by-time interaction, and prespecified covariates, including age, sex, body weight, and baseline SMM. A participant-level random intercept will account for within-participant correlation arising from repeated measurements. Time will be modeled as a categorical variable to avoid imposing a linear change trajectory. The primary effect will be estimated from the group-by-time interaction at week 24, and the adjusted between-group mean difference, 95% confidence interval, and two-sided P value will be reported.

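### The sentence naming the primary estimator (week-24 group-by-time interaction) contradicts the protocol's own definition of the primary effect, because baseline SMM is a covariate and not a level of time

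*Protocol article*

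**What the plan says.** All of the model text is in the protocol article, Statistical analysis.

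- Target: the primary effect is the "adjusted between-group difference in change in SMM from baseline to the end of the 24-week intervention".
- Response: a linear mixed model is fitted "with post-randomization SMM measurements as the dependent variable".
- Terms: "Fixed effects will include group, time, the group-by-time interaction, and prespecified covariates, including age, sex, body weight, and baseline SMM", plus a participant random intercept.
- Time: "Time will be modeled as a categorical variable to avoid imposing a linear change trajectory". No reference visit is named.
- Estimator: "The primary effect will be estimated from the group-by-time interaction at week 24".
- Reporting, in the same sentence as the estimator: "the adjusted between-group mean difference, 95% confidence interval, and two-sided P value will be reported".

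The visits are given under Procedure: "outcome assessments will be conducted at weeks 8, 16, and 24, with week 24 defined as the end of the intervention", and "A final follow-up assessment will be conducted at week 48". The levels of time in the response are therefore weeks 8, 16, 24 and 48. The section names R 4.4.2 as the software and makes SMM the only confirmatory outcome, tested at two-sided 0.05.

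**The concern.** A group-by-time interaction measures a difference in change from baseline when baseline is one of the time levels in the response. Here it is not: baseline SMM sits on the right-hand side and the first modelled visit is week 8. With a separate group main effect, the week-24 interaction measures how the treatment effect at week 24 departs from the effect at another visit, or from an average over visits. An analyst who reads off the coefficient the sentence names would report a different quantity from the one the section defines.

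This matters because it is the trial's only confirmatory test. On the literal reading, the sooner the intervention works, the smaller the tested quantity. The sample size was built on the full difference in mean change, so its power does not carry over to that coefficient.

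**Working it through.** **1. The plan's own figure.** Inputs from Sample size: difference 1.19 kg, SD 2.70 kg, two-sided alpha 0.05, power 0.80, 1:1 allocation. d = 1.19/2.70 = 0.4407, stated as 0.44. A two-sample t test (noncentral t) with d = 0.44 needs 83 per group (power 0.8045); the unrounded d needs 82. 83/(1 − 0.20) = 103.75, so 104 per group and 208 in total. The stated figures reproduce. They refer to the full 1.19 kg.

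**2. What the interaction is.** Let e_t be the adjusted group difference at week t. Given baseline SMM as a covariate, the difference in week-24 SMM and the difference in change to week 24 are the same number, so the defined effect is e24.

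| Coding of time, group main effect in the model | Group main effect | Group-by-week-24 term |
|---|---|---|
| Week 8 as reference (R's default if levels follow visit order) | e8 | e24 − e8 |
| Sum-to-zero | average of e8, e16, e24, e48 | e24 − that average |
| Week 24 as reference | e24 | does not exist |

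In none of these is the week-24 interaction e24. With week 8 as reference, e24 is the sum of the two terms.

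**3. Power of the correct contrast**, with 83 per arm and e24 = 1.19 (normal approximation).
- SD 2.70: SE = 2.70·√(2/83) = 0.419; 1.19/0.419 − 1.96 = 0.88; power 0.81.
- Baseline-adjusted SD = 2.70·√(1 − 0.50²) = 2.34: SE = 0.363; 1.19/0.363 − 1.96 = 1.32; power 0.91.

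The 0.50 is the pre-post correlation in Sample size. At that value the change-score SD and the single-visit SD are equal, if the SD is the same at both visits.

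**4. Power of the literal interaction (week 8 as reference).** SE = 2.70·√[2(1 − ρ)·2/83], with target 1.19 − e8. The documents give neither ρ (the correlation between the week-8 and week-24 values) nor e8. Both are assumptions and are varied.

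| ρ | SE | e8 = 0 | e8 = 0.40 | e8 = 0.595 | e8 = 1.19 |
|---|---|---|---|---|---|
| 0.3 | 0.496 | 0.67 | 0.36 | 0.22 | 0.05 |
| 0.5 | 0.419 | 0.81 | 0.47 | 0.30 | 0.05 |
| 0.7 | 0.325 | 0.96 | 0.69 | 0.45 | 0.05 |
| 0.9 | 0.187 | 1.00 | 0.99 | 0.89 | 0.05 |
| Expected estimate (kg) | | 1.19 | 0.79 | 0.595 | 0 |

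Here 0.40 is 1.19·8/24 (linear onset) and 0.595 is half of 1.19. With SD 2.34 in place of 2.70, the ranges over the same ρ are 0.46 to 1.00 for e8 = 0.40 and 0.28 to 0.96 for e8 = 0.595.

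**5. Simulation of the stated model** (random intercept, maximum likelihood, residual SD 2.34, ρ = 0.7, 60 trials per scenario, so illustrative only).
- e8 = 0.595: mean interaction 0.65, significant in 67%; mean week-24 contrast 1.20, significant in 88%.
- e8 = e24 = 1.19: mean interaction 0.06, significant in 3%; mean week-24 contrast 1.20, significant in 88%.

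**The case against.** The strongest reply is that the section largely says the right thing. It defines the effect correctly, and the sentence in question goes on to promise an adjusted between-group mean difference, which is not the usual name for a difference of differences against week 8. It never says that a single coefficient will be read off. The wording may be loose shorthand for the week-24 contrast taken from a model that contains the interaction. This stands. A reader might infer that the trial will test the change in effect since week 8, but the article does not support that: it fixes no reference visit, and the reporting clause points the other way.

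Three further limits stand.
- A reader might take a single power figure, such as 0.47, as the trial's real power. It rests on an assumed onset and an assumed correlation, and the range is wide. Only the case of a full effect by week 8 does not depend on the correlation.
- Putting baseline in the response is not the only way to make the interaction equal e24. A model with time and group-by-time but no separate group term would also do so. The protocol lists the group term, which rules that form out here.
- For the secondary outcomes the section names no interaction estimator. It promises adjusted differences from an analogous model, so the problem reaches them only through that word.

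The reply does not remove the contradiction. The named estimator and the defined effect are different quantities under every standard coding that keeps the listed terms.

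**Conclusion.** The estimator sentence is wrong for the model stated and should be corrected. What is established is an inconsistency between the estimator and the defined effect in the sole confirmatory test, which leaves two defensible estimates and P values. It is not established that the analysis will be run wrongly.

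The size depends on the reading. If the week-24 contrast is meant, nothing is lost and power is about 0.81 to 0.91 at 83 per arm. If the interaction is taken literally with week 8 as reference, it equals the defined effect only when there is no effect at week 8, and its expected value is zero when the effect is complete by then. A higher correlation between visits can restore power for intermediate onsets, but it does not restore the target. All power figures assume the plan's 1.19 kg and SD 2.70 (or 2.34 after baseline adjustment) and 83 participants per arm with data at the visits compared.

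**What to change.** Replace the estimator sentence with: *The primary effect is the model-based adjusted between-group difference in SMM at week 24 (group main effect plus group-by-week-24 interaction), with its 95% CI and two-sided P value.* The formula in brackets presumes week 8 as the reference level, so state that too. Add that the analogous secondary-outcome models use the same visit-specific contrast.

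An optional alternative, not required, is to move baseline SMM into the response with a common baseline mean in both arms and keep the interaction wording.

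The cost is one or two sentences. Data collection, the defined effect and N = 208 do not change. Recruitment is already under way (Trial status), so the change should be dated and made before database lock, while the analysts are still blinded.

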## Methods

### Study design

This single-blind, two-arm randomized controlled trial is designed to evaluate the effects of a knowledge graph-based lifestyle recommendation system on skeletal muscle mass, grip strength, skeletal muscle mass index, body fat percentage, physical function, and quality of life in patients with SO. Participants will be randomly assigned in a 1:1 ratio to either the intervention group or the control group. The intervention group will receive a 24-week lifestyle intervention aimed at increasing muscle mass and reducing weight, while the control group will receive conventional treatment and health education without personalized recommendations from the system. The total study duration is 48 weeks, comprising a 24-week intervention period followed by a 24-week follow-up period. Assessments will be conducted at baseline and at weeks 8, 16, 24, and 48, with week 24 marking the end of the intervention. Thereafter, both groups will enter a follow-up phase without systematic intervention and will be observed until week 48. The randomization sequence will be generated by a statistician using a computer-generated block randomization with block sizes of 4 or 6. Allocation concealment will be ensured through a password-protected centralized network system accessible only to independent registrars not involved in outcome assessment after completion of baseline assessments. Because of the nature of the lifestyle intervention, blinding of participants and intervention implementers is not possible. However, outcome assessors and statistical analysts will remain blinded throughout the study. All outcome assessments will be completed by uniformly trained independent assessors unaware of group allocation. Data managers and statistical analysts will remain blinded until database lock. Participants will be instructed not to disclose their group allocation to assessors, and an emergency unblinding procedure will be established if required. Intervention reporting will follow the Template for Intervention Description and Replication (TIDieR) checklist. The study protocol is developed in accordance with the SPIRIT statement (S1 File). Fig 1 and Fig 2 illustrate the proposed study timeline and procedures.

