Secondary outcomes will include handgrip strength, skeletal muscle index, body fat percentage, SPPB score, and SF-36 quality-of-life score. Each secondary outcome will be analyzed using a linear mixed-effects model analogous to that used for the primary outcome. Fixed effects will include group, time, the group-by-time interaction, and prespecified covariates, including age, sex, body weight, and the baseline value of the corresponding outcome. Adjusted between-group differences, 95% confidence intervals, and two-sided P values will be reported. SMM will be the only primary confirmatory outcome, whereas secondary outcomes will provide supportive evidence regarding intervention effects. For analyses involving multiple secondary outcomes and repeated time points, the Benjamini–-Hochberg procedure will be applied to control the false discovery rate.

All available repeated-measures data will be included in the linear mixed-effects models using maximum likelihood estimation under the missing-at-random assumption. The extent, timing, and pattern of missing data, together with reasons for withdrawal or intervention discontinuation, will be summarized by group. For the primary outcome, a sensitivity analysis will be conducted using multiple imputation by chained equations. The imputation model will include randomized group, age, sex, height, body weight, BMI, baseline SMM, available follow-up SMM measurements, and other variables potentially associated with missingness or the primary outcome. Twenty imputed datasets will be generated and analyzed using the primary analysis model, with estimates pooled according to Rubin’s rules. If missingness in the primary outcome is substantial or the missing-data mechanism remains uncertain, a tipping-point analysis based on delta-adjusted multiple imputation will be performed. In this analysis, a series of prespecified unfavorable shifts will be applied to the imputed SMM values to assess the robustness of the primary conclusions under plausible missing-not-at-random assumptions.

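### Naming maximum likelihood rather than REML for the mixed models makes the standard error of the week-24 difference about 1 to 2% too small; a minor point that a few words put right

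*Protocol article*

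**What the plan says.** All places are in the protocol article.

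- **Estimator.** The missing-data paragraph of Statistical analysis says the mixed models use all available repeated measurements, "using maximum likelihood estimation under the missing-at-random assumption". The sentence covers the primary model and the secondary models built on the same pattern. REML is not mentioned.
- **Model.** The primary outcome, skeletal muscle mass (SMM), is fitted by a mixed model to its follow-up values. The mean structure is given in one sentence: "Fixed effects will include group, time, the group-by-time interaction, and prespecified covariates, including age, sex, body weight, and baseline SMM". For the correlation between visits the model has one random intercept per person and nothing further, and visits enter as categories instead of a straight-line trend.
- **Visits.** Under Study design, "Assessments will be conducted at baseline and at weeks 8, 16, 24, and 48".
- **Primary quantity.** The target is described in these words: "The primary effect will be estimated from the group-by-time interaction at week 24". What will be presented for that contrast is then listed: "the adjusted between-group mean difference, 95% confidence interval, and two-sided P value will be reported".
- **Imputation.** The sensitivity analysis fits the primary model to each of twenty imputed data sets.
- **Size.** The Sample size section requires 83 per group and enrols 104 per group, 208 in total.

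**The concern.** ML divides residual sums of squares by the number of units. REML divides by the residual degrees of freedom. The stated model has six between-participant parameters (intercept, group, age, sex, body weight, baseline SMM), plus the time and group-by-time terms. ML therefore understates both the between-participant and the within-participant variance, and the standard errors inherit the shortfall.

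The shortfall favours significance, and it falls on the only confirmatory P value. The same estimator supplies the secondary intervals, the P values that enter the Benjamini–Hochberg procedure, and the within-imputation variances of the sensitivity analysis. The usual reason to choose ML over REML, comparing mean models by likelihood, does not apply to the primary contrast, whose fixed effects are set in advance.

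**Working it through.** **The plan's own figure.** An exact two-sample t test with d = 0.44, two-sided 0.05, gives 83 per group (power 0.8045). Unrounded 1.19/2.70 = 0.4407 gives 82. Then 83/(1 − 0.20) = 103.75, so 104 per group and 208 in total. The sample size reproduces. It supplies the two values of N used below: 2 × 83 = 166 and 2 × 104 = 208.

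**Inputs.**
- From the document: N = 166 or 208; six between-participant parameters; T = 4 post-baseline visits (weeks 8, 16, 24, 48), or T = 3 if week 48 is left out.
- Assumed: balanced complete data, a correct random-intercept model, and an intraclass correlation (ICC) from 0.5 to 0.9.

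**Formulas.** Set the total variance to 1. The variance of the adjusted week-24 difference is then proportional to the sum of two parts:
- between-participant part: B = ICC + (1 − ICC)/T
- within-participant part: W = (1 − ICC)(1 − 1/T)

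These add to 1. ML multiplies B by (N − 6)/N. It multiplies W by (N − 2)/N, because it divides by N(T − 1) instead of (N − 2)(T − 1). So

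SE ratio, ML to REML = √[B(N − 6)/N + W(N − 2)/N].

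With the normal reference held fixed, the size of a nominal 5% test becomes 2[1 − Φ(1.96 × ratio)].

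**Worked case, ICC 0.7 and T = 4.** B = 0.7 + 0.3/4 = 0.775 and W = 0.3 × 0.75 = 0.225.
- N = 166: 0.775 × 160/166 + 0.225 × 164/166 = 0.969; square root 0.9845.
- N = 208: 0.775 × 202/208 + 0.225 × 206/208 = 0.975; square root 0.9877.

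**Range (SE ratio, with size of the nominal 5% test).**

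| N | T | ICC 0.5 | ICC 0.7 | ICC 0.9 |
|---|---|---|---|---|
| 166 | 3 | 0.9858 (5.33%) | 0.9842 (5.37%) | 0.9826 (5.41%) |
| 166 | 4 | 0.9864 (5.32%) | 0.9845 (5.37%) | 0.9827 (5.41%) |
| 208 | 3 | 0.9887 (5.26%) | 0.9874 (5.30%) | 0.9861 (5.33%) |
| 208 | 4 | 0.9891 (5.25%) | 0.9877 (5.29%) | 0.9862 (5.32%) |

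Moving from ML to REML therefore raises the standard error by a factor between 1/0.9891 = 1.011 and 1/0.9826 = 1.018.

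**Bare week-24 group-by-time coefficient.** Only the within-participant part enters, so the ratio is √[(N − 2)/N]: 0.9940 at N = 166 (size 5.14%) and 0.9952 at N = 208 (5.11%).

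**Simulation check** (T = 4, 20,000 replicates per setting, Monte Carlo SE about √(0.05 × 0.95/20,000) = 0.15 percentage points).

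| N | ICC | SE ratio | Rejection, ML with normal reference | Rejection, REML with critical value 1.9748 |
|---|---|---|---|---|
| 166 | 0.5 | 0.9863 | 5.47% | 5.00% |
| 166 | 0.8 | 0.9836 | 5.55% | 4.99% |
| 208 | 0.5 | 0.9891 | 5.25% | 4.76% |
| 208 | 0.8 | 0.9869 | 5.42% | 4.95% |

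**Separating the two causes.** In the limiting case where all the variance lies between participants, and taking N − 6 degrees of freedom:
- REML with a normal reference: 5.17% (N = 166) and 5.14% (N = 208).
- ML with a t reference: 5.43% and 5.34%.
- ML with a normal reference: 5.61% and 5.48%.

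So part of the excess in the simulated 5.25 to 5.55% comes from the normal reference, not from ML.

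**The case against.** The strongest reply is that this is too small to report. A P value near 0.05 moves by about 0.001 to 0.004, and many analysts would treat ML against REML as preference at this sample size. The smallness stands, and it sets the weight of the point.

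The phrase also sits in a sentence about missing data, where maximum likelihood is sometimes loose shorthand for likelihood-based estimation, REML included. That is possible. As written, however, the sentence names the estimator with the smaller variances, and the same edit settles the matter either way.

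Two stronger readings are tempting, and the document supports neither.

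- **A reader might infer that the trial's true error rate is above 5%, by up to 5.5%.** The document states no reference distribution, so the upper figures, which also need a normal reference, cannot be charged to ML. The calculation also rests on balanced data and an exactly correct random-intercept structure, while the plan expects 20% dropout. A random intercept imposes equal variance at every visit. If the week-24 variance differed from the pooled value, that error could outweigh the ML shortfall and go either way. Nor was the pooled variance after imputation, or the robust-variance sensitivity analysis, calculated.
- **A reader might infer that the absence of a degrees-of-freedom method is itself a fault.** That detail can properly be left to a statistical analysis plan, which is not shown here.

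It is also too strong to say that ML has no use in this plan. The subgroup analyses add group-by-time-by-subgroup terms with several degrees of freedom. A likelihood-ratio test of those terms would need ML.

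**Conclusion.** The point holds as a minor one. The plan names an estimator that, with its own fixed effects, understates the standard error of the reported week-24 difference by about 1.1 to 1.8%; the last digit depends on whether ML or REML is the base. If the primary effect is read as the bare interaction coefficient, the shortfall is about 0.5 to 0.6%. The effect of ML alone on a nominal two-sided 5% test is to raise it to about 5.1 to 5.4%, under the balance, covariance and ICC assumptions listed above. It could change a conclusion only for a P value within a few thousandths of 0.05. The sample size and the estimand are not affected.

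**What to change.** In the missing-data paragraph of Statistical analysis, replace maximum likelihood estimation with restricted maximum likelihood (REML) estimation. Apply it to the primary and secondary models and to the primary model fitted to each imputed data set. Keep ML only for any likelihood-ratio test of fixed effects, such as the subgroup interactions. A Satterthwaite or Kenward–Roger reference is the natural companion and can be named in the statistical analysis plan.

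The cost is a few words and intervals 1 to 2% wider. REML uses the same data and is equally valid under missing at random. The Trial status section says recruitment is still open, so the wording can be settled before any analysis.
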